## **Work Package 2: Health economy analysis**

As PN is a major contributor to the healthcare costs of critically children and the clinical outcome is not yet known, an extensive health economic analysis will be included in the study planning. The economic analysis will be performed from a health care perspective and will be estimated for the period during hospitalization OR one year after admission?. The economic evaluation will be performed in accordance with the Dutch guidelines (27).

First, we will calculate and compare the direct medical costs of early versus late PN.

Real medical costs will be calculated by multiplying the volumes of health care use with the corresponding unit prices. Based on the analysis of the patients' detailed invoices, we will allocate healthcare costs into 8 categories (per diem hospitalization costs, honoraria, pharmacy costs, clinical chemistry costs, radiology costs, blood products, graft products, miscellaneous), representing the different reimbursed services and products during ICU and hospital stay. These cost categories have been validated in the health economic analysis of the adult EPaNIC study.

The drug costs will be analyzed using the first level of the World Health Organisation (9) Anatomical Therapeutic Chemical (ATC) classification. We hypothesize that antimicrobials (class J) are the determining driver for differences in pharmacy costs. This is based on the idea that late PN will reduce the incidence of new infections in the ICU.

A model will be constructed to estimate the hypothetical cost difference between early PN and late PN if all acquisition costs related to PN would have been chargeable. This modeling is important to make the results interpretable for readers in different healthcare systems. PN is in variable proportions charged to the patient directly, the hospital or the insurers. Therefore, the data from Rotterdam and Leuven will be converged to one hypothetical system of PN billing.

Costs for inpatient days in hospitals will be estimated as real, basic costs per day using detailed hospital administrative information. For the calculation of other medical costs, we will use charges as published in Dutch guidelines as a proxy of real costs (27).

All analyses will be performed on an intention-to-treat basis. The cost differences between early and late PN will be analyzed using the Mann–Whitney U test. Since cost data per patient (but not per day care) are typically highly skewed, we use nonparametric bootstrap techniques to derive a 95% confidence interval for the differences in distributions of the direct medical costs.

Furthermore, we will explore whether late PN is cost-effective compared to early PN. This will be assessed by calculating the incremental cost-effectiveness ratio (ICER), defined as the difference in costs of late versus early PN, divided by the average change in effectiveness. The primary effect measure is number of patients with a prevented new infection in ICU. Secondary outcome measure is quality of life as measured by validated questionnaires. Overall utility scores for population-based quality of life will be obtained and expressed as QALY's. QALY's will be calculated by multiplying the utility of a health state by the time spent in this health state.

Cost-effectiveness of late PN as compared to early PN will be analyzed as the difference in PN costs per patient with a prevented new infection in ICU. In the ideal scenario late PN will result in an improvement of the clinical outcome as well as

a reduction of the healthcare costs. If late PN conveys a clinical improvement at a higher cost, this cost effectiveness in three health care systems will be important to guide the respective governmental health care departments into the decisions of the reimbursement of PN.

For the health economic analysis we will collaborate with the finance & accounting and pharmacy departments of the three participating hospitals. Template database structures will be set-up in advance during the enrolment of the patients in the trial to allow an efficient health economic analysis in the framework of the study.

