## 14. OBJECTIVES

The ultimate aim of this project is to answer the question whether insufficient EN should or should not be supplemented with PN early in the disease course of critical illness in children.

The scientific objectives of the study are divided into 3 main work-packages (WP 1-3) and are the following:

- WP1: Performing and completing the first well-designed and sufficiently powered, multicentre RCT to test the effects of early PN supplementation on the health of critically ill children. The short-term outcome analysis, as well as a substantial part of the long-term follow-up, will be completed within the time frame of the study.
- WP2: an economic evaluation, in which costs and cost-effectiveness will be investigated of early versus late PN supplementation during hospitalization.
- WP3: Starting to unravel potential mechanisms that underlie any difference in acute and long term outcome with early or late PN supplementation by studying metabolic, endocrine, inflammatory and (epi.)genetic markers in the blood of critically ill children included in the study.

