## 16. TREATMENT OF SUBJECTS

### 16.1 Investigational treatment

The treatment, or intervention, in our study is best described as withholding PN in the early course of disease to reach currently recommended energy and protein intakes, when enteral delivery of these intakes is insufficient. In both allocation groups of the study, patients will be evaluated on a day to day basis to see which amount of enteral intake can be provided. The “early PN” group will receive current standard nutritional practice, which prescribes that PN should be added to EN as soon as possible in the course of disease, to achieve energy and protein goals. In the “late PN” group, we will wait to add PN, when EN is insufficient, until day 7.

[figure not shown]

“Late PN”, the so-called “intervention-group”.

In Leuven, Rotterdam and Edmonton patients randomised to the “late PN” group will receive a mixture of Glucose 5% and NaCl 0.9% at, respectively, 60% and 40% of the total flow rate that is required to obtain standard optimal hydration taking into account the volume of EN that is being delivered. If enteral feeding of at least 80% of the calculated calories is not possible after 7 days in ICU, PN, as specified below, is initiated on day 8.

The infusions will be supplemented with micronutrients and vitamins as they would have received when provided PN.

When the blood glucose levels fall spontaneously below 50 mg/dl, the standard glucose of 5% in the late PN group will be switched to 10% glucose until blood glucose level is above 80 mg/dl. At this point the infusion of glucose 10% will be stopped and switched again to glucose 5%.

Early PN", this nutritional regime is the standard therapy in the participating centres and therefore accounts as the "control-group".

All centres will use their current pharmaceutical nutritional products for enteral as well as parenteral nutrition. The differences between the products provided by the different pharmaceutical companies are small clinically irrelevant differences in glucose, lipid and protein intakes.

Despite the different pharmaceutical companies, nutritional regimes from all participating centres will be aiming for the same energy and protein targets.

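### Work Package 2 gives two different numerators for cost-effectiveness, does not name the mean cost difference as the target of inference, and leaves the time horizon open

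*Supplement*

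**What the plan says.** The economic evaluation is described in the final protocol, section 18.1.2, Work Package 2. The SAP contains no economic analysis and settles none of what follows.

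- **Scope of costs.** "The economic analysis will be performed from a health care perspective". The text continues: "First, we will calculate and compare the direct medical costs of early versus late PN". Costs are sorted into eight categories covering ICU and hospital stay.
- **First numerator.** The ICER is "defined as the difference in costs of late versus early PN, divided by the average change in effectiveness". The primary effect measure is patients with a prevented new ICU infection.
- **Second numerator.** In the next paragraph, cost-effectiveness "will be analyzed as the difference in PN costs per patient with a prevented new infection in ICU".
- **Cost comparison.** "The cost differences between early and late PN will be analyzed using the" Mann–Whitney U test. Because costs are skewed, a nonparametric bootstrap 95% confidence interval is added. Its stated target is differences in distributions of direct medical costs; the mean is not named.
- **Horizon.** Costs "will be estimated for the period during hospitalization OR one year after admission", and the sentence ends in a question mark. Section 14 describes the work package as an evaluation "in which costs and cost-effectiveness will be investigated of early versus late PN supplementation during hospitalization".

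**The concern.** The plan's two rules answer different questions. The first, read with the stated perspective, counts all care. The second, read literally, counts only feeding costs. Since the randomised intervention is itself the withholding of PN, the second numerator mostly measures the intervention and leaves out what might offset or add to it: ICU days, antimicrobials and complications. The same section expects antimicrobials to drive pharmacy-cost differences, and section 15.4 powers the trial for length of stay.

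Two further gaps leave room for choice after the data are seen. An ICER uses mean costs, but the named test compares ranks and the named interval does not say which feature of the distributions it estimates. The horizon is still a drafting question.

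At stake is a result that the plan intends as guidance to governments on reimbursement. As written, an analyst could follow either numerator and report ratios of opposite sign.

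**Working it through.** **1. Is a PN-only difference predetermined?** In the late arm, if enteral feeding is insufficient after seven days, "PN, as specified below, is initiated on day 8" (section 16.1). The SAP (Methods, Context) confirms no PN in week 1 for that arm and the same PN rule in both arms afterwards. Hence

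PN-only cost difference (late − early) = price per PN-day × (extra late-arm PN-days after day 7 − early-arm PN-days in week 1).

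This is positive only if the extra late-arm days after day 7 exceed the days avoided in week 1. That is possible, for example if late PN prolonged stay, but unlikely.

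**2. Can the choice of numerator change the sign?** The planned effect is 20% to 15% (section 15.4), so the denominator is 0.05, or 720 × 0.05 = 36 infections prevented per arm. As a check on that input, the power for 20% versus 15% with 720 per arm is 70.5% two-sided and 80.3% one-sided, matching the stated 70% and 80%.

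The documents give no prices. Assume 50–200 euro per PN-day, 1–5 PN-days avoided per patient, equal PN after day 7, and a change in all other costs of −1,000 to +1,000 euro per patient.

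- PN-only ratio = −(price × days)/0.05
- All-cost ratio = (−price × days + other)/0.05

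| Price (euro/day) | Days avoided | Other costs (euro) | PN-only ratio | All-cost ratio |
|---|---|---|---|---|
| 50 | 1 | +1,000 | −1,000 | +19,000 |
| 100 | 3 | −1,000 | −6,000 | −26,000 |
| 100 | 3 | 0 | −6,000 | −6,000 |
| 100 | 3 | +1,000 | −6,000 | +14,000 |
| 200 | 5 | −1,000 | −20,000 | −40,000 |
| 200 | 5 | +1,000 | −20,000 | 0 |

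Over the grid the PN-only ratio runs from −1,000 to −20,000. The all-cost ratio runs from −40,000 to +19,000. The signs differ whenever other costs rise by more than price × days, that is by more than 50 to 1,000 euro per patient.

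**3. Does the rank test address the mean?** Assumed lognormal costs, 720 per arm, 500 runs. Arm A has log-mean 0 and log-SD 1; arm B has log-SD 1.3. The mean ratio B/A is exp(μ + 1.3²/2)/exp(0.5), where μ is arm B's log-mean.

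| μ in arm B | Mean ratio B/A | Median ratio B/A | Mann–Whitney p < 0.05 |
|---|---|---|---|
| 0 | 1.41 | 1.00 | 6.6% |
| −0.15 | 1.22 | 0.86 | 65.8% |
| −0.345 | 1.00 | 0.71 | 99.8% |

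In the middle row a randomly chosen patient in A costs more than one in B with probability 0.536, so the ranks point to B as cheaper although its mean is 22% higher. The test can be silent about a large mean difference, significant with none, or point the other way.

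**4. Horizon.** The objectives say hospitalisation, and the cost categories are tied to ICU and hospital stay. The same work package plans QALYs as utility multiplied by time in a health state. Child health questionnaires are compared at 3 and 12 months after discharge (section 18.1.2, Work Package 1, item g), and section 18.3 makes that follow-up conditional on additional funding. No period for the QALYs is stated.

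**The case against.** The strongest reply is that PN costs is loose wording for the costs of the two PN strategies. The ICER sentence speaks of costs without restriction, direct medical costs are collected in eight categories, and the text after the PN-cost sentence foresees better outcomes at a higher cost, which hardly fits a PN-only numerator. This makes the all-cost reading the likelier intention. It does not remove the contradiction: the section refers separately to acquisition costs related to PN, and nothing says which definition governs.

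A reader might infer that the PN-only figure favours late PN by construction, or that the analysis cannot come out against it. The documents do not support that. PN from day 8 means the difference need not be negative, the ratio still depends on the infection difference, and the plan expressly allows for higher cost.

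On the rank test, the planned bootstrap interval answers much of the criticism, and the test does not feed the ICER. The size of any conflict also depends on the scenario. With log-SD 1.1, 95% of late-arm costs multiplied by 0.88 and 5% by 5, the mean rises 9% (0.95 × 0.88 + 0.05 × 5 = 1.086). Over 3,000 runs the test then favoured late PN significantly in only 15%, and the mean difference was significant in 11%. What stands is narrower: the target of the interval should be named.

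On the horizon, the objectives do give one, so it is inconsistent rather than absent.

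**Conclusion.** The point holds as a problem of specification. Two numerators are stated, they can give ratios of opposite sign, and neither the protocol nor the SAP says which applies. The literal PN-only version is at odds with the health care perspective and very likely, not certainly, favours late PN. The euro figures are illustrations under assumed prices, PN-days, equal PN after day 7 and a 5-point infection effect; they show that the sign can change, not what the trial would find. The simulations rest on assumed lognormal costs and show only that Mann–Whitney does not test the mean difference.

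The work package is secondary and exploratory. The primary endpoints and the safety analyses are unaffected. The change should be made, but the matter is of moderate weight.

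**What to change.** In section 18.1.2, Work Package 2:

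1. Define one ICER numerator: the difference in mean total direct medical cost per patient, late minus early. Report PN cost as a labelled component, and remove the sentence that makes it the cost-effectiveness measure.
2. Make the bootstrap 95% interval for the mean cost difference the main cost inference. Resample cost and effect together, and report the joint cost–effect pairs or an interval for the ICER. Keep Mann–Whitney at most as descriptive.
3. Replace the open question with the hospitalisation horizon of section 14 for cost per infection prevented. State separately the period over which QALYs are computed, consistent with the questionnaires at 3 and 12 months and their dependence on funding.

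Items 1 and 2 are wording only: the eight cost categories and the bootstrap are already planned. Item 3 needs one decision on the QALY period and no new data on hospital costs.

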### **Work Package 3: Mechanistic analyses in relation to short- and long-term outcome**

#### ***Impact of early versus late PN on infection and the inflammatory response***

The incidence of new, ICU-acquired, infections is a primary efficacy endpoint in the presented study. Based on the results of the adult EPaNIC study (1), we anticipate a lower infection rate with late PN as compared with early PN. We will investigate whether differences in leukocyte function could explain in part such effect. Therefore, blood samples will be taken at pre-set time points during ICU stay for the isolation of monocytes and granulocytes to assess their chemotactic, phagocytosis and oxidative burst capacity (17, 18). Antimicrobial defense depends on, amongst others, efficient clearance of intracellular pathogens in the autophagic pathway (xenophagy) (10). Indeed, inactivation of autophagy in macrophages and neutrophils has been shown to increase susceptibility to infection. It has previously been demonstrated an autophagy-deficiency phenotype in liver and skeletal muscle of fed prolonged critically ill patients (11). Importantly, a recent study in prolonged critically ill rabbits demonstrated a role for early PN in suppression of the autophagic pathway during critical illness (19). If autophagy would be similarly compromised in leukocytes by early PN, such effect may contribute to a reduced incidence of infections with late PN. We will address this question in a subset of well-matched patients. We will also measure the p62 protein levels of isolated white blood cells obtained upon admission and on day 3 and 7 in ICU, which is known to accumulate when autophagy is deficient/insufficient, as well as the LC3-II/LC3-I ratio as a marker of mature autophagosome formation (20-22). In addition, we will isolate leukocyte DNA from all patients to investigate whether genetic predisposition by single nucleotide polymorphisms (SNPs) in genes of the autophagic core machinery may play a role in susceptibility to infections and whether any such SNP would interact with the nutritional approaches of the study design. The autophagy pathway and/or proteins also appear to play a crucial role in the control of inflammatory signaling and regulation of inflammatory transcriptional responses (10). In this regard, it has been shown that increased levels of p62 activate the pro-inflammatory transcription factor NF- $\kappa$ B. We will study the impact of early versus late PN on pro- and anti-inflammatory cytokines (interleukin-1beta (IL-1beta), IL-2, IL-4, IL-5, IL-6, IL-8, IL-10, tumor-necrosis-factor-alpha, interferon-gamma).

#### ***Impact of early versus late PN on the neuroendocrine axes***

Critical illness is hallmarked by striking alterations in the hypothalamic-pituitary-peripheral hormone axes (neuroendocrine axes), according to a biphasic pattern (23). The peripheral effector hormone levels are reduced in both phases of critical

illness, although the etiology is different with peripheral target organ resistance in the acute phase and relative hypopituitarism in the prolonged (chronic) phase.

The hypothalamic-pituitary-adrenal axis shows a biphasic, but somewhat different response as compared with the other axes, with cortisol as effector hormone being high in both phases. The responses of the neuroendocrine axes during prolonged critical illness overall have been linked to the development of a characteristic hypercatabolic state, resulting in feeding-resistant muscle wasting, and the severity of the disturbances has been associated with the high risk of morbidity and mortality of the patients. Not only excessive activation of the hypothalamic-pituitary-adrenal axis, but also adrenal insufficiency contributes to morbidity in critically ill children (24).

It was previously hypothesized that strict blood glucose control with intensive insulin therapy would mildly reactivate the somatotrophic and thyrotrophic axes and anabolism in critically ill children in view of a larger functional capacity of the hypothalamus and pituitary, and the higher amount of nutrition they receive as compared with adult critically ill patients. Unexpectedly and despite improved ICU outcome, however, this therapy further suppressed the somatotrophic axis and increased the urea/creatinine ratio as a marker of catabolism (25). Also the low-T3 syndrome could not be reversed by this therapy (unpublished data).

Unpublished data obtained in a rabbit model of prolonged critical illness suggest that relative fasting during critical illness reduces (peripheral) activation of the somatotrophic and thyrotrophic axes with lower levels of insulin-like growth factor-I (IGF-I) and triiodothyronine (T3) levels, but also attenuates the rise in the stress hormone cortisol as compared with moderate dose intravenous feeding during critical illness. These findings urge a thorough analysis of the impact of early versus late PN on these neuroendocrine axes in the critically ill children included in our study. We hypothesize that late PN results in suppression of the neuroendocrine axes, in concert with the intensive insulin therapy. Unlike conventional belief, we also hypothesize that such suppressed neuroendocrine axes during prolonged critical illness could be associated with a beneficial acute and long-term clinical outcome.

We will evaluate the activation of the somatotrophic axis in the acute and chronic phase of critical illness by measuring the levels of growth hormone (GH), acid-labile subunit (ALS), IGF-I and its binding proteins (IGFBP-1 and IGFBP-3), the activation of the thyrotrophic axis by analysis of thyroxine (T4), T3, reverse T3 (rT3) and thyroid stimulating hormone (TSH), and the adrenal axis by adrenocorticotrophic hormone (ACTH) and cortisol. The metabolism of cortisol will be studied further by the relative levels of its metabolites excreted in urine (26) and by collecting hair samples for the long term cortisol levels. The impact of early versus late PN on the neuroendocrine axes will be studied in relation to markers of catabolism, muscle volume and strength, as well as clinical outcome. The clinical outcome will be assessed during follow-up consultations that are held in the departments that have referred their patients to the ICU in Leuven and Rotterdam.

### ***The epigenetics of early versus late PN***

It has been known since a long time that dietary exposures can have health consequences years or decades later. E.g. the later health of babies who were in the womb during the Dutch famine in the winter of 1944 was greatly affected by the caloric restriction of their mothers. The children of pregnant women exposed to famine were shown to be more susceptible to chronic adult diseases such as diabetes, obesity and cardiovascular disease. Apparently, the short period of caloric

restriction can be “remembered” by the body further on in life. There is a growing body of evidence that epigenetic mechanisms mediate this memory. Epigenetic mechanisms alter the gene expression without changing the primary DNA sequence. Rather the epigenetic mechanisms work through DNA methylation, histone

modifications and non-coding microRNAs. During the clinical trial, biological material (spun-down cells from whole blood samples) will be collected from the study patients to compare these epigenetic changes between the early and late PN treatment groups. The mechanistic findings will be correlated with the acute and the long-term outcome of the critically ill study patients.

### **18.1.3 Other study parameters**

#### ***Safety endpoints***

Safety endpoints comprise vital status, hypoglycemia, SAEs and complications related to the mode of nutrition. Survival up to 90 days after randomization in both treatment groups will be compared by Kaplan Meier survival plots. The impact of “late PN” versus “early PN” will be analyzed, with and without correction for risk factors, by Cox proportional hazard analysis. In addition, we will record in-ICU and in-hospital mortality, and will analyze differences with Chi-square testing. As the randomized study intervention only takes place during a time window up to the 8th day in ICU, we also plan to analyze early lethality within this time window in the intention-to-treat population as part of the safety analysis.

As patients not receiving early PN may be considered at increased risk for hypoglycemia, we will report for both groups the number of patients experiencing hypoglycemia <40 mg/dl during the time window of the randomized intervention. Hypoglycemia resistant to parenteral glucose administration is considered as a SAE and the incidence during the time window of the randomized intervention will be reported for both groups. In addition, overall blood glucose control during the time window of the intervention will be compared using daily morning blood glucose as well as daily maximal and minimal blood glucose.

Safety issues also comprise the occurrence of feeding-mode-related complications during the time window of the intervention. Therefore, occurrence of these complications (digestive intolerance, complicated insertion of feeding tubes, pneumothorax, haemothorax and subclavian or carotid artery puncture, occlusion or displacement of central venous catheters or gastric feeding tubes) will be reported for both treatment groups.

